**Fig. 5 Fig5:**
[figure not shown]
Consort diagram

We will use a staggered parallel cluster randomized design [23] (Fig. 6), with cohorts initiating REP and enhanced REP in 9-month intervals. Staggering is necessary to create cohorts sized for optimal training and EF within project resources. Sites are not blinded to implementation strategy assignments.

**Fig. 6 Fig6:**
[figure not shown]
Staggered parallel clustered randomized trial design to assess implementation outcomes

### Evaluation of CTI’s implementation and effectiveness

We plan a mixed-method evaluation of CTI’s implementation and effectiveness, to (a) capture fidelity to REP and enhanced REP; (b) compare CTI fidelity and sustainment achieved by REP versus enhanced REP; (c) compare quality metrics (housing stability, hospitalizations and other service use, and veteran and case manager experience) achieved by the two strategies and by CTI; (d) compare costs and return on investment (ROI) for CTI and the two implementation strategies; and (e) assess contextual factors that affect fidelity, sustainment, and quality metrics. Below, we describe the methods for each of these goals, followed by the methods for qualitative data collection and analyses that cut across goals.

### Implementation strategy fidelity

Fidelity to REP and enhanced REP will be assessed in three domains: [24] adherence (the extent to which strategies took place), dose (proportion of providers receiving each strategy), and responsiveness (provider receptivity to and involvement in strategies).

We will develop and maintain an Implementation Activity Log that summarizes all activities pertaining to REP and enhanced REP. The log will include dates and times of all training, TA, and EF sessions; participants; and templated notes on the implementation process. Adherence to REP and enhanced REP will be assessed by comparing the log to the processes described in the implementation strategies above. The dose will be captured by describing the frequency of TA/case consultation and EF sessions delivered to each site (and % of eligible participants attending). Responsiveness will be characterized by analyzing data from log notes, periodic reflections [25] (brief, ethnographically informed, guided discussions that capture near-real-time snapshots of implementation context), and semi-structured interviews with aftercare staff at 12 months post-implementation.

### CTI fidelity

We will measure site-level CTI fidelity 12 months after REP initiation, capturing adherence to CTI’s core components in the 6 months prior to measurement. We will employ methods adapted from a study of CTI for homeless adults leaving shelters [22] and developed with experts who have measured CTI fidelity across RCTs [22, 26]. Fidelity assessors will use a roster of HEVs engaged at implementation sites to randomly select 5 HEVs (“exemplars”) on each case manager’s caseload. Videoconferences with each case manager will be used to complete a templated review form by reviewing charts from these exemplars. Data from the exemplar review template will be used by the fidelity assessors to complete and score an adapted version of the CTI Implementation Self-Assessment Tool [27], which has cut-offs for adequate versus inadequate fidelity. We will use the *t*-test to compare fidelity between sites receiving REP versus enhanced REP.

These scores will be integrated with analyses of semi-structured aftercare staff interviews at 12 months and periodic reflections; qualitative data will glean staff perceptions of CTI fidelity. Within and across implementation strategies, we will compare sites with quantitative scores indicating adequate versus inadequate fidelity and use targeted coding of qualitative data to explore contextual factors associated with fidelity ratings.

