**Methods:**

We will use the Replicating Effective Programs (REP) implementation strategy to support CTI implementation at 32 sites selected by our partners. Half (*n*=16) of these sites will also receive 9 months of external facilitation (EF, enhanced REP). We will conduct a type 3 hybrid cluster-randomized trial to compare the impacts of REP versus enhanced REP. We will cluster potential sites into three implementation cohorts staggered in 9-month intervals. Within each cohort, we will use permuted block randomization to balance key site characteristics among sites receiving REP versus enhanced REP; sites will not be blinded to their assigned strategy. We will use mixed methods to assess the impacts of the implementation strategies. As fidelity to CTI influences its effectiveness, fidelity to CTI is our primary outcome, followed by sustainment, quality metrics, and costs. We hypothesize that enhanced REP will have higher costs than REP alone, but will result in stronger CTI fidelity, sustainment, and quality metrics, leading to a business case for enhanced REP. This work will lead to products that will support our partners in spreading and sustaining CTI in aftercare.

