## Methods

### Overview

We hypothesized that enhanced REP will have higher implementation costs than REP, but enable increased tailoring to local contexts that results in stronger CTI implementation and effectiveness, supporting a business case for enhanced REP. To test this hypothesis, we will use a type 3 hybrid implementation-effectiveness trial [13]; this design tests the impacts of implementation strategies while gathering data regarding an EBP’s impacts on clinical outcomes. Specifically, we will compare the impacts of REP versus enhanced REP on CTI implementation and sustainment, while observing CTI’s effectiveness on housing and health outcomes. In a cluster randomized design, we will assign 32 aftercare sites to REP (*n*=16) versus enhanced REP (*n*=16), clustering sites in three implementation cohorts staggered in 9-month intervals.

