### Implementation strategy: Replicating Effective Programs (REP)

Housing Transitions QUERI will use REP at 32 aftercare sites to implement CTI. REP is a bundle of implementation strategies with a strong evidence base and precedent of feasibility within VA [20, 21]. REP uses stakeholder input to facilitate packaging, training, and TA of EBPs; we selected REP because it resembles “usual care” mental health EBP rollouts in VA. Our use of REP is intended to enhance case managers’ CTI skills and clinical competency, thereby strengthening CTI fidelity and sustainment. REP is particularly well-suited for CTI implementation; research shows that adapting and packaging CTI and its trainings and TA for program and population contexts, using stakeholder input, is critical for effective, high-fidelity implementation [22].

Figure 3 depicts REP’s phases and each phase’s products, specified for this project. Phases one and two (“pre-conditions and “pre-implementation”) were completed in our implementation pilot. Phases three and four comprise the focus of this protocol. Phase three (“implementation”) will encompass national delivery of the CTI package to 32 sites, with iterative refinement informed by our implementation evaluation. Phase four (“maintenance and evolution”) will include booster sessions, modeled on prior CTI rollouts. This final phase of REP also includes assessing financial factors and organizational changes needed for CTI sustainment.

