### Study design

We plan a type 3 hybrid implementation-effectiveness trial [13], registered as NCT05312229 on April 4, 2022, and determined to be non-research by VA’s Central Institutional Review Board. Given distinct leadership, staffing, and policies by site, and the high likelihood of contamination among case managers within sites, cluster randomization will occur at the site level. Within each cohort, the implementation team will use permuted block randomization—with geographic setting (urban, suburban, and rural) and number of case managers (a proxy for site size and resources) as stratification factors—to balance these factors among sites receiving REP versus enhanced REP. Figure 5 depicts a Consolidated Standards of Reporting Trials (CONSORT) flow diagram of our comparison groups. We will also use the stratification factors to match each of the 32 implementation sites to a control aftercare site not implementing CTI. Data from control sites will be used to assess selected quality metrics and costs of CTI as implemented. The CONSORT 2010 checklist of information for randomized controlled trials is available as supplemental material.

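### The primary t-test on site fidelity omits the cohort and stratification factors used to randomize; if these predict fidelity, it is conservative and gives up precision

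*Protocol article*

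**What the plan says.** All references are to the protocol article.

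- **Outcome.** The Abstract (Methods) says "fidelity to CTI is our primary outcome, followed by sustainment, quality metrics, and costs". The CTI fidelity section says "We will measure site-level CTI fidelity 12 months after REP initiation", so each site contributes one score.
- **Analysis.** The same section says "We will use the *t*-test to compare fidelity between sites receiving REP versus enhanced REP". It mentions no covariate, stratum or cohort term.
- **Randomization.** Study design says "Within each cohort, the implementation team will use permuted block randomization", "with geographic setting (urban, suburban, and rural) and number of case managers (a proxy for site size and resources) as stratification factors". The Abstract gives the purpose: "permuted block randomization to balance key site characteristics among sites receiving REP versus enhanced REP".
- **Size.** Overview plans 16 sites per arm. Participating sites gives 10–11 sites in each of three cohorts. The Discussion says that the funder set the number of sites and that no power analysis was behind it.
- **Cohorts.** They start 9 months apart. The REP section says that the CTI package will be delivered "with iterative refinement informed by our implementation evaluation".

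**The concern.** The analysis does not follow the randomization. Blocking and stratification are meant to make the two arms alike on cohort, setting and number of case managers. A two-sample t-test takes no credit for that balance. Whatever variance in fidelity these factors carry stays in its error term, and any imbalance that remains by chance is not corrected.

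There are reasons to think that the factors could matter. The package is refined as the cohorts proceed, and sites join a cohort when they judge themselves ready. CTI is delivered in the field, which may differ between urban and rural areas. The protocol itself treats the number of case managers as a stand-in for resources. These are reasons to expect some association, not evidence of its size.

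What is at stake is the precision of the primary comparison. No sites can be added, so the analysis is one of the few places where precision can still be gained.

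**Working it through.** **Inputs from the protocol.** 32 sites, 16 per arm; three cohorts of 10–11 (11/11/10 in the simulation); three settings; one fidelity score per site. The protocol gives no power, effect size or SD for fidelity, so there is no stated figure to reproduce.

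**Assumptions.** A two-sided 5% level (stated only for the housing outcome); permuted blocks of 2; number of case managers in two levels; R² = the share of between-site fidelity variance explained by cohort, setting and size. The protocol gives none of the last three, so R² is varied.

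**Step 1: the t-test as planned.** Degrees of freedom are 16 + 16 − 2 = 30. The noncentrality is d × √(16/2) = 2.83d. Power reaches 80% at d = 1.02 SD and 90% at d = 1.18 SD.

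**Step 2: why it can be conservative.** If the factors were perfectly balanced, the true standard error of the difference would be √(1 − R²) times the one that the t-test uses. At R² = 0.20 the t-test's standard error would be too large by a factor of 1/√0.80 = 1.12, and at R² = 0.40 by 1/√0.60 = 1.29. These are upper limits, because balance will not be perfect.

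**Step 3: the adjusted model with perfect balance.** The terms are intercept 1, strategy 1, cohort 2, setting 2 and case managers 1, so residual df = 32 − 7 = 25. The noncentrality becomes 2.83d/√(1 − R²). The difference detectable with 80% power is 1.03 SD at R² = 0, 0.98 at 0.10, 0.92 at 0.20 and 0.80 at 0.40. On this calculation adjustment breaks even at R² of about 0.014. That is optimistic, because it ignores the precision lost when strategy and covariates are not exactly balanced.

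**Step 4: simulation with chance imbalance.** Blocks of 2 within cohort × setting × size; t-test against linear regression with 5 covariate df; true difference 1.0 SD. Ranges cover repeated runs.

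| R² | Power, t-test | Power, adjusted | Difference (points) | Type I error, t-test |
|---|---|---|---|---|
| 0 | 78–79% | 75–76% | −2 to −3 | 4.7–4.9% |
| 0.10 | 78–79% | 79% | 0 to +1 | 4.4% |
| 0.20 | 79–80% | 83–84% | +4 to +5 | 3.3–3.5% |
| 0.40 | 80–81% | 92–93% | +11 to +12 | 1.9–2.3% |

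The adjusted model's type I error was 4.5–5.0%. With 3,000 trials, the Monte Carlo standard error of a power near 80% is √(0.8 × 0.2/3,000) = 0.7 points. The break-even therefore lies near R² = 0.10, not 0.014.

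**Step 5: sensitivity to the scheme.** Stratifying by cohort × setting only, with a difference of 1.02 SD, gives much the same picture: 80% against 77% at R² = 0, 82% against 81% at 0.10 and 79% against 84% at 0.20. Blocks of 2 in 3 × 3 × 2 = 18 cells (32/18 = 1.8 sites each) do not force 16 against 16, and about 73% of simulated trials departed from it. This matters little: a 14/18 split multiplies the variance by (1/14 + 1/18)/(1/16 + 1/16) = 0.1270/0.1250 = 1.016.

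**The case against.** The strongest reply is that nothing here is invalid. The site is the unit of both randomization and analysis, so clustering is respected, and the type I error can only fall below its nominal level. This stands: the point concerns efficiency, not validity.

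A reader might go further and infer that the t-test wastes power as a matter of fact. The documents do not support that. They show that the team wanted balance on these factors, not that the factors explain a given share of fidelity variance. At about 10% there is nothing to gain, and below that adjustment loses slightly. A reader might also infer that the t-test makes a missed benefit more likely than its nominal power suggests. It does not: its simulated power stays at 78–81% throughout. What is given up is a possible gain.

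That cohort affects fidelity is also inference. The first two REP phases were completed in the pilot, and every cohort is measured at the same point, 12 months after REP initiation. Refinement of the package need not move the scores.

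Finally, this is a condensed article, and a statistical analysis plan may add adjusted analyses; the text does not rule them out. That carries limited weight, because the article does name the test for the primary outcome and the test named does not follow the randomization.

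**Conclusion.** The point holds in conditional form. The stated primary analysis ignores cohort, geographic setting and number of case managers, by which the sites are randomized. The t-test remains valid. If these factors predict site fidelity, it is conservative and gives up precision that more sites cannot restore.

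The balance of gain and loss favours adjustment: at most about 3 points of power lost if the factors are irrelevant, against about 4–5 points gained if they explain 20% of the between-site variance and about 12 if they explain 40%. These figures rest on the assumed block size, size categories, 5% level and 1.0 SD difference, and the true share explained is unknown. The change is therefore advisable rather than essential, and confidence that it would raise power in this trial is moderate.

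**What to change.** Before any fidelity data are seen, name as the primary analysis a site-level linear regression of the 12-month fidelity score on assigned strategy, cohort (three levels), geographic setting (three levels) and number of case managers (one linear term). Report the adjusted mean difference with a 95% confidence interval and t-based inference. Keep the t-test as a sensitivity analysis, and use the same model for the 18-month score described under CTI sustainment.

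Use main effects only. A term for every combination of cohort, setting and size would need 18 or more cells for 32 sites and would use up the degrees of freedom.

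The cost is a sentence or two of text and 5 degrees of freedom (30 to 25), which is roughly 3 points of power if the factors turn out to be unrelated to fidelity. Fixing the model in advance also avoids a later choice between adjusted and unadjusted results.

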### CTI sustainment

We will repeat our fidelity assessment 18 months after the start of implementation as a measure of CTI sustainment at 6 months after implementation supports cease. These scores will be integrated with analyses of semi-structured interviews with aftercare staff at 18 months and periodic reflections to explore perceptions of sustainment and contextual factors associated with sustainment across sites and implementation strategy assignment.

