GPD National Program Office policy leaders identified critical time intervention (CTI) as an evidence-based, structured, and time-limited case management model that—if implemented nationally—would standardize and improve aftercare case management. There are five randomized controlled trials (RCTs) [5–8] and a systematic review [9] demonstrating that CTI effectively improves housing and decreases hospitalizations among homeless-experienced adults. Moreover, CTI was successfully implemented in 8 VA facilities for HEVs with serious mental illness, suggesting it is feasible and appropriate for VA scale-up and spread. CTI is also well-aligned with aftercare, which was designed to improve housing stability among HEVs undergoing housing transitions. However, implementing EBPs in community-based organizations serving HEVs brings challenges [10, 11].

This paper describes the protocol for the Housing Transitions Quality Enhancement Research Initiative (QUERI), which will implement CTI across 32 aftercare sites nationally and compare the impacts of two implementation strategies on effectiveness and implementation outcomes. To implement and sustain CTI, we will use the Replicating Effective Programs (REP) implementation bundle to enable sites to achieve fidelity to CTI’s core components, while accommodating adaptations to fit the diversity of aftercare contexts. REP includes EBP packaging, staff training and technical assistance, process evaluation and feedback, and ongoing maintenance support [12]. Half of these sites (*n*=16) will receive an “enhanced REP” bundle in which REP is augmented by 9 months of EF, a process of providing tailored support for providers and leaders to adopt and incorporate EBPs into routine care. We will provide our partners with evidence regarding the comparative impacts and costs of REP vs. enhanced REP for CTI implementation and sustainment across diverse aftercare contexts, including sites with quality gaps.

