Online CTI toolkit, including recorded training sessions, the CTI manual, clinical templates and tools, and relevant resources	As needed by any aftercare case manager or supervisor
On-demand case consultation process with a CTI expert via telephone or videoconference (30 min/consultation)	As needed—requested by any aftercare case manager or supervisor, up to once/month per aftercare site
Community of practice sessions delivered via synchronous videoconference (1 h/session)	Monthly for 6 months, starting the month after the 6-session initial CTI training is completed
Listserv to facilitate sharing of clinical practices and anonymized case discussion among aftercare case managers and supervisors across sites	As needed by any aftercare case manager or supervisor
CTI booster sessions delivered via synchronous videoconference (1 h/training)	Every 3 months, beginning 9 months after the start of CTI implementation

Last, we developed and pilot-tested EF materials and processes. EF is a flexible implementation strategy involving deliberate and interactive problem-solving and support for providers to implement EBPs. In our pilot, a facilitator trained in CTI and facilitation provided tailored support that built the sites’ organizational capacity to implement CTI and empowered case managers to enact systems-based change toward CTI implementation [19]. After each session, the facilitator completed a templated form to summarize the call, engage in self-reflection, delineate facilitation strategies used, and highlight barriers faced in employing these strategies. Data from these forms were used to create a CTI facilitation guide.

Qualitative data from this pilot suggested that most aftercare case managers were highly satisfied with CTI and comfortable using this practice with HEVs. Post-training, case managers reported that CTI was acceptable and credible, with strong data for its effectiveness. Though case managers struggled with the time-limited (6 months) aftercare duration, there was consensus that CTI was a compatible and useful model in this context. Funding was obtained to proceed to a 32-site national implementation and evaluation.

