**Fig. 4 Fig4:**
[figure not shown]
REP vs. enhanced REP, as experienced by sites

We selected EF to enhance REP because it is a powerful tool, based on organizational theory, that can assist with organizational change by addressing site-specific implementation barriers. In our pilot, we found that tailored support for site-specific challenges was important for CTI implementation. In Housing Transitions QUERI, EF will be delivered by facilitators who are social workers trained in CTI and facilitation. EF sessions (30 min/week videoconferences) will begin within 2 weeks of aftercare staff completing initial CTI training and continue through month 9 of CTI implementation. The content of sessions will vary by sites’ needs and contextual factors; facilitators will employ the guide developed in our pilot, using real-time data and quality improvement techniques to identify steps that sites can follow to implement CTI.

Throughout, facilitators will engage in the implementation and support-oriented activities (Table 2). Though facilitators are trained in CTI, they do not provide CTI clinical support or case management training; clinical and training needs are referred to the REP team.

**Table 2 Tab2:** Sample external facilitation activities

Implementation-oriented activities	Support-oriented activities
• Identify CTI implementation challenges and apply rapid-cycle improvement processes to address these challenges • Use VA administrative data to rapidly monitor outcomes (e.g., service use) of Veterans on a case manager’s caseload and provide feedback to aftercare staff • Educate aftercare staff and VA aftercare liaisons and identify key VA and community resources • Develop a site-specific CTI implementation plan	• Build relationships with aftercare staff • Encourage CTI practice and implementation • Educate aftercare staff on external facilitation, including its benefits and roles • Engage with and develop a plan to routinely update local change agents and other key stakeholders on CTI implementation • Ensure resources and personnel are available to grow and/or adapt CTI as needed

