#### Costs of implementation strategies

We will compare the costs of using REP versus enhanced REP for spreading and sustaining CTI. We conceptualize the adaptation of CTI to aftercare as a fixed, non-repeatable cost that will not be included in our analyses. Most costs associated with the spread stage of implementation are fixed, repeated with each cohort, including CTI initial training, communities of practice, and toolkit maintenance; these costs will be assessed by cohort. Variable spread costs that depend on the number of sites per cohort include case consultation and EF; these will be assessed by the site. With respect to sustainment, the quarterly booster sessions and re-training of new case managers at the participating implementation sites are repeatable fixed costs. Case manager turnover will be tracked using the national roster of aftercare participants per case manager.

All implementation activities of our team will be tracked through the Implementation Activity Log. In addition, to capture time spent by the implementation team on session preparation or documentation (i.e., time that is not captured in the Implementation Activity Log), team members will complete cost capture templates weekly during the second implementation cohort. Implementation activity log and cost capture template data will be linked to hourly costs per team member.

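### The 18-month score is labelled sustainment six months after supports end, but no support in the protocol text ends at month 12 and quarterly boosters have no stated end

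*Protocol article*

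**What the plan says.** Protocol article, CTI sustainment: the fidelity assessment is repeated "18 months after the start of implementation as a measure of CTI sustainment at 6 months after implementation supports cease". The method is that of the CTI fidelity section, where each score looks back over 6 months.

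The supports are described elsewhere in the article:

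- **EF** (enhanced REP only). Weekly sessions start within 2 weeks of the end of initial training and "continue through month 9 of CTI implementation" (Implementation strategy: enhanced REP).
- **Community of practice.** Monthly for 6 months, from the month after training (Table 1).
- **Boosters.** "Every 3 months, beginning 9 months after the start of CTI implementation" (Table 1). No last session is given.
- **Case consultation, toolkit, listserv.** Available as needed, with no end given (Table 1).

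Three further places describe support as continuing. The Background lists among REP's elements "process evaluation and feedback, and ongoing maintenance support". The REP section says "Phase four (“maintenance and evolution”) will include booster sessions, modeled on prior CTI rollouts". Costs of implementation strategies says "With respect to sustainment, the quarterly booster sessions and re-training of new case managers at the participating implementation sites are repeatable fixed costs".

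On time zero, the CTI fidelity section says "We will measure site-level CTI fidelity 12 months after REP initiation", while the sustainment section counts from the start of implementation. Table 1 puts the 6-week training at the start of implementation. Footnote b of Table 4 puts the baseline interview after training but before implementation.

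**The concern.** Sustainment is named directly after the primary outcome in the abstract, appears in Aim 2, and feeds the business case and playbook meant for all 128 aftercare sites. Its label makes a specific claim: the score is taken six months after support has ended. The article gives no end date that produces that interval, and it describes boosters and re-training as activities of the sustainment period itself.

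What is at stake is interpretation. Fidelity that holds with no support and fidelity that holds with a quarterly booster are different findings. Partners deciding whether to keep paying for boosters need to know which one the trial observed.

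**Working it through.** **Step 1: the cessation date that the label implies.** Assessment month minus stated gap: 18 − 6 = month 12.

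**Step 2: the gap from each support's end to month 18.** The 6-week training is taken as about 1.5 months. The community-of-practice end is shown for both possible clocks.

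| Support | End in the text | Gap to month 18 |
|---|---|---|
| EF | month 9 | 18 − 9 = 9 months |
| Community of practice, clock from end of training | about month 6 | 18 − 6 = 12 months |
| Community of practice, clock from start of training | about 1.5 + 6 = month 7.5 | 18 − 7.5 = 10.5 months |
| Boosters | not stated | see step 3 |
| Consultation, toolkit, listserv | not stated | cannot be computed |

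No support with a stated end gives 6 months.

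**Step 3: boosters.** Every 3 months from month 9 gives months 9, 12, 15 and 18. The gap depends on which is last:

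- last at month 9: 18 − 9 = 9 months
- last at month 12: 18 − 12 = 6 months
- last at month 15: 18 − 15 = 3 months
- last at month 18: 18 − 18 = 0 months

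The stated 6 months is reproduced only if boosters stop after month 12 and consultation also stops by then. The text states neither.

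**Step 4: what the score covers.** With a 6-month look-back, the month-18 score covers months 18 − 6 = 12 to 18. If boosters continue, month 15 lies inside that window. Month 12 is its opening edge and month 18 coincides with the assessment. So one 1-hour session is strictly inside and two are at the boundary.

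**Step 5: the two ways to read the label.** If boosters count as implementation supports and continue, supports have not ceased at month 18. If boosters are a separate sustainment activity and as-needed resources are set aside, the last scheduled support is EF in enhanced-REP sites (9 months earlier) and community of practice in REP sites (about 10 to 12 months earlier). Neither reading gives 6, and the second gives a different interval in each arm.

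**Step 6: time zero.** Table 1 places training inside implementation and Table 4 footnote b places it before. The two clocks differ by the length of training, about 6 weeks. EF's end and the 18-month score are both counted from CTI implementation, so the 9-month gap does not depend on which clock is chosen, provided the same one is used for both.

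**The case against.** **The label refers to supports in the plural, so the last one to end sets the date.** This stands. EF ending at month 9 does not by itself contradict a six-month gap, and boosters at months 9 and 12 only would give exactly 6. But that schedule has to be stated, and the cost section's treatment of boosters and re-training points the other way.

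**Figures 4 and 6 may give the end dates.** They depict site activities and the staggered design and are not available here. This limits certainty about the missing end date. If they do show one, the prose and Table 1 should agree with it.

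**The outcome and the comparison are sound.** A reader might infer that the 18-month score fails as an outcome or that the arm comparison is biased. The article does not support that. The score is the same fidelity measure taken at month 18. Boosters belong to REP, which both arms receive, so the contrast is still EF versus no EF. No power or alpha figure depends on this point.

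**Costs.** A reader might infer that booster costs would be left out of the business case. They would not: the cost section counts boosters and re-training, and Table 5 lists the boosters.

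**EF duration.** A reader might infer from Table 1 that EF runs for well under 9 months. That holds only if the clock starts with training. If it starts after training, as Table 4 footnote b has it, EF fits 9 months.

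**Time zero is minor.** REP initiation and the start of implementation can be read as one event, and a 6-week shift applies to both arms alike. This is fair, and the point is secondary.

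**Conclusion.** The point holds as a labelling and interpretation problem that should be fixed. The interval in the sustainment definition cannot be derived from any support end date in the text. If boosters continue as Table 1 and the cost section suggest, the 18-month score reflects CTI fidelity under continued low-intensity REP maintenance in both arms, and in enhanced-REP sites 9 months after EF ended. The support-free interval would then be 0 months at month 18, against the 6 stated.

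The comparison of REP with enhanced REP remains valid at month 18. It addresses whether any advantage from EF lasts while REP maintenance goes on. It cannot show that CTI persists once support is withdrawn.

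This rests on three assumptions: boosters continue past month 12, the 18-month score uses the same 6-month look-back as the 12-month score, and the figures not shown do not set a month-12 end for all supports. If the last of these is wrong, the repair is only to state that end date in the text.

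**What to change.** 1. Reconcile Table 1, the REP section, the enhanced REP section, CTI sustainment, Costs of implementation strategies and Figures 4 and 6, so that each support has one stated end, or is stated to be ongoing.
2. Unless all supports stop at month 12, relabel the 18-month outcome as CTI fidelity under continued REP maintenance, 9 months after EF ended, and limit the sustainment conclusion to that.
3. Report, by arm, the boosters, consultations and re-training that sites received in months 12–18. The Implementation Activity Log is already planned to hold the dates and participants of training and technical assistance sessions.
4. Define one time zero, say whether the 6-week training falls before or after it, and use it for both fidelity assessments and for EF.

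The cost is protocol wording and one descriptive table. No new data collection is needed, and neither the randomization nor any sample-size statement changes.
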